### Patient population and recruitment procedure

Patients of fellowship trained arthroplasty surgeons at two institutions will be identified as potentially eligible for the study based on 40 kg/m^2^ < BMI < 47 kg/m^2^ recorded in the patient’s medical record within the last 6 months and recommended primary, unilateral total knee or hip arthroplasty. For patients identified as potentially eligible while in clinic, an orthopaedic surgeon will introduce the patient to the study, and a member of the research team (research assistant or trainee) will conduct an eligibility screening and obtain verbal consent either in-person or by phone. For patients identified as potentially eligible outside of clinic, a member of the research team will call the patient to introduce the study, and conduct eligibility screening and consent on the phone.

Eligible, interested, and consented patients will be provisionally enrolled, and all subjects will be shipped a standard bathroom scale to their home (Fig. 1). This initial enrollment is provisional, as subjects will be required to verify enrollment BMI by (a) submitting a photo to the study team of their study scale during a weigh-in that displays their body weight, or by (b) recording a baseline weight at an onsite healthcare facility within 2 weeks of provisional enrollment. Once enrollment BMI is verified to be 40 to 47 kg/m^2^, subjects will be fully enrolled and randomized to the intervention arm or clinical standard of care arm via REDCap. Subjects will be given a $40 check for enrolling, which includes (1) taking a baseline survey, (2) recording the baseline weight at an onsite healthcare facility or with a home study scale, and (3) getting baseline labs within 2 weeks of the baseline weight. Baseline weights will be recorded without shoes or outer clothing (e.g., coats). All subjects will be given a $20 check if they can verify a mid-study weight during week 6 of the study by recording a weight at any onsite healthcare facility or by submitting home study scale photos. All subjects will receive a $40 check for completing an end-of-study survey, weight, and labs at 10–14 weeks after enrollment.

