### Arms

Intervention participants will download a telemedicine online/smartphone app (Nutrimedy, Brookline, MA, USA) and be connected at enrollment with a certified registered dietitian who will contact intervention participants weekly or bi-weekly via video calls and unlimited in-app text messaging for up to 3 months. The first week will include either one 55-min video session or two 25-min sessions. Weeks 2–4 will have weekly 25-min video calls, and weeks 5–12 will have biweekly 25-min sessions for a total of 8–9 sessions over 12 weeks. Together, participants and dietitians will come up with goals for the 12 weeks, and dietitians will check on progress toward these goals using in-app tools such as food logs and messaging between video calls. All patients will be encouraged to lose at least 20 pounds with a goal BMI < 40 kg/m^2^ after 12 weeks.

Dietitians will use principles of motivational interviewing, cognitive behavioral interventions, and the socioecological model to remotely provide behavior and lifestyle interventions. Motivational interviewing is a patient-centered, collaborative approach to counseling in which the dietitian elicits personally relevant reasons from subjects to make behavior changes that may promote weight loss. Dietitians and patients then structures goals for lifestyle modifications around these personal motivations [17]. Cognitive behavioral interventions provide subjects with strategies to change cognitive processes to alter behaviors, such as self-monitoring (e.g., recording food intake, weight, and exercise), stimulus control (e.g., keeping less healthy foods in cabinets out of sight), and accountability by having frequent check-ins with dietitians [18]. The socioecological model proposes that multiple levels of influence including intrapersonal (e.g., knowledge and attitudes), interpersonal (e.g., family and friends), and community factors (e.g., organizations, workplaces, neighborhoods) can impact energy-balance behaviors and weight outcomes [19]. Dietitians will promote the adoption and maintenance of behaviors across multiple levels of influence.

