#### Primary outcome measurement

The primary outcome will be weight change at 12 weeks (10–14 weeks) after study enrollment. Weights will be recorded at an onsite healthcare clinic or by home study scales.

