### Sample size calculation

The 2016 paper by Gandler et al. found a pre-operative dietitian intervention before TJA resulted in a weight loss of − 3.38 kg (standard deviation [SD] 6.62) versus a weight gain of + 2.01 kg (SD 6.45) in the usual care group [13]. Using 80% power to detect a difference between weight loss of − 3.38 kg in the intervention group versus + 2.01 kg weight gain in the usual care group with SD 6.62 kg, this study would require 24 patients per arm. Thus, we will aim for 30 participants in each arm to allow for 25% dropout.

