### Statistical analyses

The main statistical analysis will be performed via an intention-to-treat analysis. Per protocol sensitivity analysis (completing at least half or four video calls) will also be performed. The significance level for statistical tests will be set at *p* ≤ 0.05. Baseline characteristics between the two groups will be assessed using t-tests for continuous variables and chi-square or two-tailed Fisher’s exact tests (when required by small cell counts) for categorical variables. Differences over time in continuous variables between the intervention and clinical standard of care group, such as percent weight change, body weight, and BMI, will be analyzed using *t* tests. Missing week 12 weight outcomes will be carried forward from week 6 outcomes when available.

We will measure feasibility via the ease of recruitment based on the ratio of enrolled subjects to the number of people approached about the study, and via maintenance of contact with a dietitian (e.g., number of video calls completed) based on study participant attrition and follow-up survey completion rates (retention). We will measure acceptability via survey items about components of the intervention, and through qualitative comments from a semi-structured interview. We will perform survey analyses using SAS (SAS Institute Inc., Cary, NC) or similar software. For most questions, participants will choose between four categories: strongly agree, somewhat agree, somewhat disagree, and strongly disagree. Assuming the distribution of responses to baseline surveys will be relatively similar, we will pool follow-up survey answers into “agree” and “disagree” for simplicity, and then conduct chi-square or two-tailed Fisher’s exact tests to examine differences between intervention and control group responses to follow-up surveys.

Qualitative data will be analyzed using the immersion crystallization method [29]. This qualitative technique includes multiple rounds of “immersion” through close readings of transcripts, followed by reflection and the “crystallization” of emerging themes. Multiple investigators will read the transcripts and arrive at a unanimous consensus concerning the emerging themes. Then, one investigator will code the transcripts to organize representative quotes.

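### Carrying the week-6 weight forward to week 12 biases the primary estimate unless dropouts' weight stops changing at mid-treatment, and no planned analysis tests that assumption

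*Protocol article*

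**What the plan says.** All references are to the protocol article.

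- **Endpoint** (Primary outcome measurement): "The primary outcome will be weight change at 12 weeks (10–14 weeks) after study enrollment".
- **Analysis set** (Statistical analyses): "The main statistical analysis will be performed via an intention-to-treat analysis". The arms are compared by t test.
- **Missing data** (same section): "Missing week 12 weight outcomes will be carried forward from week 6 outcomes when available". No value is specified for a participant who has neither weight.
- **Sensitivity analysis** (same section): "Per protocol sensitivity analysis (completing at least half or four video calls) will also be performed". No other is stated.
- **Week-6 weight** (Patient population and recruitment procedure): it is sought in both arms: "All subjects will be given a $20 check if they can verify a mid-study weight during week 6 of the study".
- **Treatment after week 6** (Arms): "weeks 5–12 will have biweekly 25-min sessions for a total of 8–9 sessions over 12 weeks".
- **Expected loss** (Sample size calculation): 30 per arm, chosen to allow for 25% dropout.

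**The concern.** Carry-forward treats the weight at the middle of a 12-week programme as if it were the weight at the end. The plan itself expects weight to keep moving: sessions run to week 12, and the upper BMI limit in the exclusion criteria is justified by a weekly rate of loss sustained over 12 weeks. For anyone imputed, the analysis therefore measures a different quantity from the stated endpoint.

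The design also makes it plausible that missingness differs by arm and is related to outcome. Participants are not blinded. Only the intervention arm has scheduled dietitian contact, and the weekly self-reported weights are asked of that arm. The safety section allows participants to be removed for rapid weight loss, which is detected through that reporting.

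What is at stake is the size of the primary effect and, if dropout is unequal, a small spurious difference when there is no true effect.

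**Working it through.** **1. The plan's own figure.** The inputs are in the Sample size calculation section: "Using 80% power to detect a difference between weight loss of − 3.38 kg in the intervention group versus + 2.01 kg weight gain", with SD 6.62 kg. The difference is 3.38 + 2.01 = 5.39 kg. The article sets the level at 0.05 without stating sidedness, so I assume two-sided.

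n = 2 × (1.960 + 0.842)² × 6.62² / 5.39² = 23.7, so 24 per arm. The stated figure reproduces.

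**2. How much treatment remains at week 6.** Week 1 has 1-2 sessions, weeks 2-4 have 3, and weeks 5-12 have 4. By week 6 about 5 of 8 or 6 of 9 sessions are scheduled (62-67%). Week 6 is halfway in calendar time but not in sessions.

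**3. Expected estimate under carry-forward.** Let pI and pC be the shares imputed in the intervention and control arms, and f the fraction of the 12-week change reached by week 6. Neither f nor the split of dropout by arm is in the article, so both are assumptions. I also assume that every dropout has a week-6 weight.

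Estimate = −3.38 × [1 − pI(1 − f)] − 2.01 × [1 − pC(1 − f)]

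If dropouts would have continued like completers, the true value is −5.39 kg:

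| Missing (intervention / control) | f = 0.5 | f = 0.75 | f = 1 |
|---|---|---|---|
| 25% / 25% | −4.72 (12% short) | −5.05 (6%) | −5.39 (0%) |
| 12.5% / 37.5% | −4.80 (11%) | −5.10 (5%) | −5.39 (0%) |
| 37.5% / 12.5% | −4.63 (14%) | −5.01 (7%) | −5.39 (0%) |

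For the first cell: 5.39 × (1 − 0.25 × 0.5) = 4.72. Equal dropout biases the estimate almost as much as unequal dropout, because the amount missing matters more than its split.

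**4. If dropouts regain weight** (f = 0.5, 25% / 25%).
- Return to baseline in both arms: the true value is 0.75 × 5.39 = 4.04 kg, and carry-forward gives 4.72, so the benefit is overstated by 0.67 kg.
- Intervention dropouts revert to the usual-care course: the true value is again 4.04 kg (0.75 × 3.38 − 0.25 × 2.01 + 2.01), with the same overstatement. At 37.5% / 12.5% the overstatement is 1.26 kg.

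**5. No true effect.** With both arms changing by −3.38 kg and f = 0.5, 10% against 35% missing gives (0.35 − 0.10) × 0.5 × 3.38 = 0.42 kg. The type I error is then about 6%. Equal dropout gives no bias here.

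**6. Precision and power** (25% / 25%, f = 0.5; assumed week-6 SD 4.7 kg and week 6-12 correlation 0.8; 30 per arm).
- Carry-forward, by simulation: mean t-test standard error 1.60 kg against an actual spread of the estimate of 1.59 kg; power 0.83.
- Likelihood model on the same incomplete data, by simulation: spread about 1.8 kg, power 0.83. Analytic check: √{2 × 6.62² × [(1 − 0.8²)/22.5 + 0.8²/30]} = 1.81 kg.
- Fully observed data: power 0.87.

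**The case against.** Several points on the other side stand.

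- **The size is assumed.** It depends on f, which the article does not give. Sessions are front-loaded, so f may exceed one half, and the bias is smaller if fewer dropouts have a week-6 weight.
- **The main scenario is modest and conservative.** The error is 0.67 kg in a 60-patient trial of feasibility and efficacy. Its direction is not assured, however, as step 4 shows.
- **The proposed model is not immune.** It relies on data missing at random. If dropouts return to baseline, it would still target 5.39 kg against a true 4.04 kg, which is 1.35 kg too large and worse than carry-forward. That is why a missing-not-at-random analysis has to accompany it.

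A reader might also infer three stronger claims that the evidence does not support.

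- **That the t-test standard error is too small.** It matches the spread of the carry-forward estimate (step 6). The fault lies in what is being estimated.
- **That carry-forward costs power.** The fall from 0.87 to 0.83 is relative to fully observed data, which no analysis can recover. The likelihood model does no better on the same data.
- **That the analysis is not intention-to-treat.** The article does not say that participants with neither weight are excluded. It only gives them no value under this rule, and a fuller document may cover them.

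Nor is unequal dropout the condition for bias in general. It is decisive only when there is no true effect.

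**Conclusion.** The concern holds. The article itself fixes the rule for its primary endpoint, so this is not a detail left to an analysis plan. The estimate is biased unless dropouts' weight stays put after week 6, or the changes happen to cancel between arms.

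With 25% missing per arm and dropouts who would have continued like completers, the planned 5.39 kg is understated by 12% at f = 0.5, by about 6% at f = 0.75, and not at all at f = 1. With regain the error reverses. Under no true effect the distortion is about 0.4 kg at 10% against 35% missing. All of this rests on assumed values of f and of the dropout split, and on every dropout having a week-6 weight.

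The per-protocol analysis selects on call attendance, so it leaves the missing-weight assumption untested. This should be fixed. It is a moderate fault in the estimate and does not invalidate the trial.

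**What to change.** Replace the carry-forward sentence with a primary analysis along these lines: a likelihood-based repeated-measures model (or multiple imputation) using the baseline, week-6 and week-12 weights of all randomised participants, with arm-by-visit terms and the week-12 contrast between arms as the primary result. State how participants with neither follow-up weight are handled.

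Add a delta- or reference-based sensitivity analysis for weights missing not at random, covering regain after dropout. Keep carry-forward, if at all, as a labelled sensitivity analysis. Settle the wording before group assignments are revealed.

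No new data are needed, since all three weights are already planned in both arms. The cost is slightly more analysis work and a somewhat wider interval: the spread of the estimate is about 1.8 kg against 1.6 kg under the assumptions above, with about the same power.

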### Quality control and safety monitoring

Prior to the clinical trial, research staff will receive protocol training to confirm that staff understand the roles and process of the trial. One RD will deliver the intervention for all intervention subjects. The RD will be certified in clinical nutrition and lifestyle counseling (credentialed Registered Dietitian [RD] by the Academy of Nutrition and Dietetics, master’s degree [MS] in clinical nutrition, Licensed Dietitian/Nutritionist [LDN], and Certified Nutrition Support Clinician [CNSC]), and will have significant experience with the mobile app used for the intervention. The RD and mobile app staff are required to complete courses in Health Insurance Portability and Accountability Act (HIPAA) awareness for healthcare providers.

The study team will contact the RD every 3 weeks to review any safety concerns. We define unsafe weight loss as greater than 20 pounds of weight loss per month. All intervention participants will be asked to submit self-reported weights weekly through the mobile app, email, or REDCap survey. The RD will be instructed to promptly alert the study team of any participants meeting this criterion so that they may be removed from the study with appropriate referrals to their primary care physician who can guide treatment after seeing them in clinic or otherwise escalate their care according to their needs (e.g., admitting them to a hospital for a comprehensive workup). AEs will be tracked and reported per institutional review board (IRB) protocol.

Adherence to the IRB-approved protocol will also be reviewed at the participant safety meetings that occur every 3 weeks with the principal investigator. The principal investigator will have ultimate responsibility for the integrity, completeness, and confidentiality of all data. Surveys will be administered and stored using REDCap, a secure HIPAA compliant and password protected web-based application, and only study personnel will have access to the research participant data. Personnel from the study team will be designated for study management, which will include periodic monitoring of the study to ensure that proper records are kept, study procedures are followed, and complete and accurate data are collected.

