### Outcome measurements

Outcome and demographic data will be collected from blood serology, chart review, mobile app user data, pre- and postintervention surveys, and phone interviews.

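### The safety rule for rapid weight loss permits removal from the study rather than from the intervention, so 12-week weights can go missing in one arm because of the primary outcome

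*Protocol article*

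**What the plan says.** All of this is in the protocol article.

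- **Trigger** (Quality control and safety monitoring): "We define unsafe weight loss as greater than 20 pounds of weight loss per month".
- **Detection** (same section): "All intervention participants will be asked to submit self-reported weights weekly through the mobile app, email, or REDCap survey". The alert comes from the single dietitian who treats the intervention arm. The standard-care arm has no weekly weights and no study dietitian. Its one mid-study weight, at week 6, is not linked to the rule.
- **Action** (same section): the dietitian alerts the study team to "any participants meeting this criterion so that they may be removed from the study with appropriate referrals to their primary care physician".
- **Outcome** (Primary outcome measurement): "The primary outcome will be weight change at 12 weeks", with a window of 10 to 14 weeks. "Weights will be recorded at an onsite healthcare clinic or by home study scales".
- **Analysis** (Statistical analyses): "The main statistical analysis will be performed via an intention-to-treat analysis". "Missing week 12 weight outcomes will be carried forward from week 6 outcomes when available".

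**The concern.** Closer monitoring of the treated arm is proportionate. The problem is the action attached to it. Stopping a treatment for safety is one decision, and ending a participant's time in the study is another. The text names the second.

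Three features combine. The trigger is a large change in weight, which is the primary outcome variable. The described detection reaches one arm only. The consequence can be the loss of the 12-week weight. Missing values that depend on the outcome in one arm bias the between-arm difference. If the lost weight stays off, those removed are among the largest losers in the intervention arm, so the bias runs toward no effect.

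The week-6 rule is a partial repair. Someone removed after week 6 is set back to an earlier weight. Someone removed before week 6 has nothing to carry forward unless a week-6 weight is still taken.

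The secondary endpoint of losing at least 20 lb is exposed too. A participant who has lost more than 20 lb from baseline has already crossed that line when the rule fires, and one such person is 1/30 = 3.3 percentage points of the arm.

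**Working it through.** **1. The plan's own figure.** Inputs from Sample size calculation: −3.38 kg against +2.01 kg, SD 6.62 kg, 80% power. Alpha is 0.05 (Statistical analyses), assumed two-sided.

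- Difference = 3.38 + 2.01 = 5.39 kg.
- n per arm = 2 × (1.960 + 0.842)² × 6.62² / 5.39² = 23.7, rounded up to 24. The stated figure reproduces.
- Two-sample t-test power with 30 per arm: noncentrality = 5.39 / (6.62 × √(2/30)) = 3.15, giving 87.3%.

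**2. The trigger in context.** 20 lb = 9.07 kg. Per week, this is 20 / 4.35 = 4.6 lb. The programme goal is 20 lb over 12 weeks, about 1.7 lb per week.

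**3. One removal.** If one of 30 has a 12-week change of −10 kg and is missing, the mean of the others is (−3.38 × 30 + 10) / 29 = −3.15 kg, a shift of 0.23 kg.

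**4. How often, and how far.** The documents give no weekly weight paths, so these were assumed and simulated (600,000 intervention paths per case).

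- The 12-week change is normal with mean −3.38 kg.
- The SD is 6.62 kg, or 5.0 kg as an assumed alternative, because 6.62 comes from a study with a one-year period (Discussion).
- A share of the variance (0, 0.25, 0.5 or 1) is a within-person random walk.
- The remaining path is linear or front-loaded (half the change by week 4).
- The rule fires at a loss above 9.07 kg within any window of up to 4 weeks.
- Everyone who triggers is removed. This is an upper bound, because the text makes removal optional.

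The comparator is what the fix would observe: the intervention stops and weight is held at its trigger value to week 12. Shift A treats removals before week 6 as missing and sets later ones to their week-6 weight. Shift B assumes that every removed participant has a week-6 weight.

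| SD 6.62 kg | Share 0 | 0.25 | 0.5 | 1 |
|---|---|---|---|---|
| Linear: % triggering | 0.02 | 0.88 | 3.2 | 11.6 |
| Linear: shift A (kg) | 0.00 | 0.06 | 0.21 | 0.78 |
| Linear: shift B (kg) | 0.00 | 0.04 | 0.15 | 0.53 |
| Front-loaded: % triggering | 1.3 | 2.0 | 3.8 | 11.6 |
| Front-loaded: shift A (kg) | 0.09 | 0.13 | 0.25 | 0.78 |
| Front-loaded: shift B (kg) | 0.00 | 0.01 | 0.07 | 0.44 |

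Shares 0 to 0.5 are taken as moderate. Share 1, a pure random walk, is an extreme case.

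**5. Sensitivity.**

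- SD 5.0 kg: shift A is at most 0.03 kg for shares 0 to 0.5, and 0.13 kg at share 1.
- Half the loss regained by week 12 (SD 6.62, shares 0 to 0.5): 0.00 to 0.04 kg.
- Those triggering at week 10 or later keep a weight in the 10–14 week window (share 0.5): shift A falls to 0.12 kg (linear) and 0.20 kg (front-loaded).
- Mean loss of 6 kg (SD 6.62, shares 0 to 0.5, weight held): 0.00 to 0.40 kg.

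**6. Effect on power.** A 0.25 kg shift leaves 5.39 − 0.25 = 5.14 kg. Noncentrality = 5.14 / (6.62 × √(2/30)) = 3.01, giving 84.1% with 30 analysed per arm, against 87.3%.

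**The case against.** The strongest reply is that this is one clause in a safety paragraph of a condensed article. It does not say that outcome weights stop or that the participant leaves the analysis. What is collected after a safety removal may be set out in the full protocol, which is not at hand. Part of this stands: the article does not state that weights cease. But it is not merely silent, because it names removal from the study as the action, and followed literally that ends follow-up.

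Second, a missing outcome does not contradict intention-to-treat, and nothing puts a removed participant outside the analysis set. That is fair. The rule undermines the intention-to-treat comparison rather than contradicting it.

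Third, a weight may still turn up. A clinic weight counts, the referral leads to a physician visit, and "Outcome and demographic data will be collected from blood serology, chart review" among other sources. This is possible, but not assured.

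Fourth, the event is remote. The trigger is nearly three times the programme's target pace, and the exclusion criteria already treat more than three pounds per week as inappropriate. Even the 810 kcal/day formula diet cited in the Discussion averaged 10.7 kg in 8 weeks, about 12 lb per 4 weeks. Removal is discretionary, and trigger rates of 3 to 4% need half the variance to be a random walk. All of this stands, and it limits the size of the point. It does not justify the wording. Discretion over who leaves, used after a large outcome change is reported in one arm, does not make the missing values ignorable.

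**Conclusion.** The concern holds, as a minor one. As written, the rule permits the loss of primary-outcome data in the intervention arm because of the outcome, and the week-6 rule only partly makes up for it.

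The number affected is unknown and may be zero. Under moderate assumed paths it is 0.02% to 3.8%, or 0 to about 1 of 30. The intervention mean then shifts by 0 to 0.25 kg, or 0 to 0.15 kg if every removed participant has a week-6 weight. The upper figure is under 5% of the planned 5.39 kg (0.25 / 5.39 = 4.6%).

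The direction, toward no effect, rests on the lost weight staying off. The size rests on the assumed paths, on an SD borrowed from a one-year study, and on removal of everyone who triggers. It is larger only under an extreme path (0.78 kg) or a larger mean loss (up to 0.40 kg at −6 kg). Rapid loss may reflect response or illness, and the point does not depend on which.

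**What to change.** Keep the threshold, the weekly weights, the dietitian's alert and the referral. In Quality control and safety monitoring, change the action from removal from the study to stopping the study intervention. Add that these participants still provide the week-6 and week 10–14 weights, by home scale or in clinic, and remain in the intention-to-treat set unless they withdraw consent.

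The cost is close to nil: a change of wording, plus weights that are already scheduled, on a scale that every participant is already sent (Patient population and recruitment procedure). Participant protection is not weakened, since continued weighing of someone losing weight quickly is itself useful for safety.
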